### Secondary aims

The secondary aims are to determine the effect of adjuvant treatment with dexamethasone on survival at 6 months, disability at 10 weeks and 6 months, the rate of sterilisation of cerebrospinal fluid (CSF), the frequency of grades 3, 4, and serious adverse events, the incidence of IRIS, the incidence of other opportunistic infections, repeated treatment for cryptococcal meningitis, the presence of visual deficit at 10 weeks, and health economics. In addition, the effect of steroids on survival by continent will be assessed.

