**Other**		
Indeterminate cerebral lesion (s)	Neurologic illness, with evidence for an intracerebral lesion by brain scan, where the differential diagnosis is either cerebral toxoplasmosis. PML, cerebral lymphoma, or HIV encephalopathy	

Based on 1993 Revised CDC classification system (MMWR 1992; 41(RR-17): 1-19) and modified for this trial.

Visual deficit (at week 10)IRISIncreased intracranial pressure (clinical or measured)

Uniform management of patients and recording of data will be ensured by the local study staff, who will do clinical assessments daily while admitted and at follow-up visits.

Disability and mortality at 6 months and evidence of morbidity (including IRIS) since last seen (week 10) will be collected with either a structured telephone interview or an outpatient visit. Outpatient visits may occur in the patient’s home when the patient cannot come to the hospital.

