#### Analysis of secondary end points

##### Neurologic disability

The disability score at week 10 and month 6 of follow-up is defined as the higher (worse) of the “simple question” and the Rankin score assessed at that time point and will be categorised as good outcome, intermediate disability, severe disability, or death (in case the patient died before the respective time point) as previously described [10] (also see Table 1). The proportion of patients with a good outcome will be compared between the two arms with a logistic regression adjusted for continent (in addition to the treatment arm). Patients lost to follow-up will be analysed according to their last recorded disability status. If the rate of patients lost to follow-up exceeds 10%, we will also perform an alternative analysis based on multiple imputation of missing values.

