##### Adverse events

The frequency of serious and grade 3 and 4 adverse reactions as well as the frequency of specific adverse events will be summarised (both in terms of the total number of events as well as the number of patients with at least one event). The proportion of patients with at least one such event (overall and for each specific event separately) will be summarised and (informally) compared between the two treatment groups based on the Fisher Exact test.

**The rate of IRIS and the rate of relapse** (defined as antifungal treatment intensification or re-treatment) will be modelled with cause-specific proportional hazards models stratified by continent, taking into account the competing risk of prior death. Cumulative incidence functions for the competing events will also be calculated and displayed by treatment arm. Secondary time-to-event end points (time to new AIDS-defining illness or death and time to new neurologic event or death) will be analysed with Kaplan-Meier curves and Cox regression models, as described for the primary end point expressed earlier. The proportion of patients with blindness or visual deficit will be compared between the two arms with a logistic regression (as for the proportion of patients with good disability described earlier).

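### Disability analysis carries the last recorded status forward as its main handling of loss, which at month 6 assumes no death or change; multiple imputation is added only above 10% loss

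*Protocol article*

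**What the plan says.** The rule stands in the Protocol article, Analysis of secondary end points, Neurologic disability. The score at week 10 and at month 6 is the worse of the Two Simple Questions and the Rankin score at that time. It has four categories: good, intermediate, severe disability, and death if the patient died before the time point. The arms are compared on the proportion with a good outcome, by logistic regression adjusted for continent.

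On missing outcomes the section says: "Patients lost to follow-up will be analysed according to their last recorded disability status". It then adds: "If the rate of patients lost to follow-up exceeds 10%, we will also perform an alternative analysis based on multiple imputation of missing values". The word *also* makes imputation an addition to carry-forward, not a replacement for it.

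Secondary aims names "disability at 10 weeks and 6 months" as the times of interest. For the later one, Clinical monitoring says: "Disability and mortality at 6 months and evidence of morbidity (including IRIS) since last seen (week 10) will be collected", by structured telephone interview or outpatient visit, which may take place at the patient's home. Analysis populations puts every randomised patient, except those mistakenly randomised without cryptococcal meningitis, into the primary population for all analyses.

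**The concern.** Carry-forward assumes that nothing changes after the last contact. That is hard to defend between week 10 and month 6. The protocol's section on 6-month survival says that most relapses fall within 6 months of diagnosis. Its section on retreatment says that some patients may be treated elsewhere and that the episode may come to light only at the 6-month contact. Death is itself an outcome category, yet carry-forward can never assign it to a patient whose death was not learned of.

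The rule also enters a guessed value as an observed one, so the confidence interval takes no account of the guess. The multiple imputation that would address this depends on a threshold whose time point and denominator are not given.

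The protocol is more careful elsewhere. Fungal decline is modelled jointly with survival because truncation by death may be informative, and IRIS and relapse are analysed with death as a competing risk. At stake is the reliability of a secondary comparison of good outcome, above all at month 6.

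**Working it through.** **Step 1: what is carried forward.**

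| Time of loss | Value used at week 10 | Value used at month 6 |
|---|---|---|
| After week 10 | observed | week-10 category, as if alive and unchanged |
| Before week 10 | no earlier disability assessment described in the text shown | the same gap |

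A patient lost before week 10 still belongs to the analysis population, so some category must be found. The trial flow diagram and flow chart are not shown, so earlier recordings cannot be ruled out.

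**Step 2: would the 10% trigger operate?** Inputs from Sample size and power considerations: hazard ratio 0.7, 80% power, two-sided 5%, 30% overall 10-week mortality.

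- Schoenfeld's formula gives 247 deaths, as stated.
- 247 / 0.30 = 823.3, rounded up to 824 patients, as stated.
- Margin for loss: 880 − 824 = 56, and 56 / 880 = 6.4%.
- Trigger, if read as overall: more than 0.10 × 880 = 88 patients.

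Loss at the level of this margin would not trigger imputation. The margin belongs to the 10-week end point; no figure is given for month 6.

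**Step 3: error within one arm.** Let *L* be the proportion lost, *c* the share of the lost carried as good, and *t* the share truly good. The error in that arm's proportion with a good outcome is *L* × (*c* − *t*). The documents give neither *c* nor *t*. With *L* = 6.4% and *c* = 0.50 assumed:

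| *t* (assumed) | Overstatement of good outcome |
|---|---|
| 0.50 | 0 points |
| 0.35 | 1.0 point |
| 0.20 | 1.9 points |
| 0 | 3.2 points |

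If some lost patients improved to good after week 10, *t* could exceed *c* and the sign would reverse.

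**Step 4: error in the difference between arms.** This is *L*₁(*c*₁ − *t*₁) − *L*₀(*c*₀ − *t*₀). All rates below are assumed.

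- Equal loss and equal net misclassification: 0.
- Loss 9% v 4%, net misclassification 0.2 in both: 0.05 × 0.2 = 1.0 point.
- Loss 9% v 4%, net misclassification 0.4 in both: 0.05 × 0.4 = 2.0 points.
- Loss 6.4% in both, net misclassification 0.3 v 0.1: 0.064 × 0.2 = 1.3 points.
- Loss 9% v 4%, net misclassification 0.3 v 0.1: 2.7 − 0.4 = 2.3 points.

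Loss of 9% v 4% averages 6.5%. It stays below 10% overall and in each arm, so imputation would not be triggered under either reading.

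**Step 5: scale.** With 440 per arm and an assumed good-outcome rate of 20% to 50%, the standard error of the difference is √(2*p*(1 − *p*)/440), or 2.7 to 3.4 points. The 95% half-width is 5.3 to 6.6 points. Counting 880 rather than 824 values as observed narrows the interval by a factor of √(824/880) = 0.968, about 3%.

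**The case against.** The strongest reply is that the effect is small and limited to a secondary end point. That is largely right. The trial is double-blind, nothing in the documents points to unequal loss, and a shift of 1 to 2 points is well inside the interval in step 5. Loss alone does not bias the difference; net misclassification is needed too. Deaths that become known are classed as deaths, and the 6-month contact by telephone, clinic or home visit should find many of them.

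Several stronger readings are tempting, but the documents do not support them.

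- *The rule is undefined before week 10.* Patients are reviewed daily in hospital and then at set visits, and the schedule figures are not shown. One can say only that the text describes no earlier disability assessment.
- *About 17 deaths would be hidden.* This multiplies 0.30 by 56. But 30% is 10-week mortality from randomisation, not mortality after week 10, and the 56 are a margin for the 10-week end point. In the good versus not-good comparison, an unseen death carried as intermediate or severe changes nothing.
- *The check that early benefit lasts is undermined.* That purpose is given for 6-month survival, which has its own Cox analysis.
- *Imputation would never be run.* Month-6 loss is not stated and may exceed 10%.
- *Visual deficit is handled in the same way.* The cross-reference, "as for the proportion of patients with good disability described earlier", qualifies the logistic regression. It names the model and does not clearly import the carry-forward rule.

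What remains is a weak main rule, with the better method held back behind a loosely worded trigger. The protocol fixes this rule itself, so it is not detail left to an analysis plan.

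**Conclusion.** The point holds for disability at week 10 and month 6. Single carry-forward is the main handling of loss, and at month 6 it treats patients lost after week 10 as alive and unchanged, against the protocol's own expectation of relapse within 6 months. Only unseen changes into or out of the good category distort the planned comparison.

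At the 6.4% loss implied by the sample size, carry-forward would be the only planned week-10 analysis; nothing can be said about month 6. The size and direction of bias cannot be derived from the documents. About 1 to 2 percentage points follows from assumed loss of 9% v 4% with net misclassification of 20% to 40%, and somewhat more if misclassification also differs by arm. The understatement of uncertainty is slight at this level of loss. The primary Cox analysis of survival is not affected. This is a worthwhile and inexpensive improvement, not a threat to the trial's main conclusion.

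**What to change.** Make multiple imputation of the four-level outcome (good, intermediate, severe, dead) the main analysis of disability at week 10 and at month 6, whatever the loss rate. Impute by arm, using baseline and follow-up data already collected, and let death be a possible imputed value for patients whose survival at the time point is unknown. Derive good versus not good from the imputed categories and fit the planned logistic regression. Keep carry-forward as a sensitivity analysis only. The 10% trigger, with its unstated time point and denominator, can then be dropped.

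Imputation rests on its own assumption: given the data used, lost patients resemble those followed. That is weaker than assuming no change at all.

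The cost is revised wording, modest extra programming and slightly wider confidence intervals. No new data are needed, and the protocol already foresees the method.

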##### Rate of CSF sterilisation during the first 2 weeks (based on available data from selected sites only)

Fungal decline in the first 14 days will be modelled with a joint model for longitudinal and survival data. The longitudinal part of the model will be a linear mixed-effects model with longitudinal log-CSF quantitative culture fungal counts as the outcome, continent and interaction terms between the treatment groups and the time since enrolment of the measurement as fixed covariates, and a random patient-specific intercept and slope. The survival part of the joint model models mortality up to 2 weeks depending on the treatment group, continent, and the patient-specific random intercepts and slopes. The survival part acts as a missing data mechanism to allow potentially informative truncation of quantitative count measurements due to death.

Longitudinal measurements of intracranial pressure during the first 2 weeks will be modelled in the same way.

##### Adverse events

The frequency of serious and grade 3 and 4 adverse reactions as well as the frequency of specific adverse events will be summarised (both in terms of the total number of events as well as the number of patients with at least one event). The proportion of patients with at least one such event (overall and for each specific event separately) will be summarised and (informally) compared between the two treatment groups based on the Fisher Exact test.

**The rate of IRIS and the rate of relapse** (defined as antifungal treatment intensification or re-treatment) will be modelled with cause-specific proportional hazards models stratified by continent, taking into account the competing risk of prior death. Cumulative incidence functions for the competing events will also be calculated and displayed by treatment arm. Secondary time-to-event end points (time to new AIDS-defining illness or death and time to new neurologic event or death) will be analysed with Kaplan-Meier curves and Cox regression models, as described for the primary end point expressed earlier. The proportion of patients with blindness or visual deficit will be compared between the two arms with a logistic regression (as for the proportion of patients with good disability described earlier).

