#### Immunosuppression

Corticosteroids are immunosuppressive. It is possible that they may slow yeast clearance from CSF, and increase the risk of other infections. However, animal studies suggest that dexamethasone improves yeast clearance from CSF [14]. Even if the rate of yeast clearance is reduced, this may not be detrimental. In this study, we will measure the rate of clearance of yeast from CSF (see Appendix 1). Patients with CM are profoundly immunosuppressed: the median CD4 count in Vietnamese patients is 16 cells/μl (which compares with a median CD4 count of 42 in Vietnamese HIV patients with tuberculous meningitis) [38]. Given this, whether dexamethasone will significantly increase the risk of other opportunistic infections (OIs) is not clear. The incidence of other OIs is a secondary end point of the study. Patients in the study will receive chemoprophylaxis against *Pneumocystis jirovecii* and other opportunistic infections, in line with national guidelines. Patients will be screened for TB at study entry as part of normal care.

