## Statistics

### Sample size and power considerations

The trial is powered for the primary end point (that is, overall survival during the 10-week follow-up period).

Few data exist on which to estimate the potential effect size of dexamethasone on mortality from CM. We have based our estimate of the effect size on data from tuberculous meningitis, which shares clinicopathologic features with CM. In a large RCT of dexamethasone to treat tuberculous meningitis in Vietnam, the hazard ratio (HR) for death was 0.69 at 9 months in favour of dexamethasone [25]. Most of this effect occurred during the first 3 months of treatment. The dose of dexamethasone we will test is the same as that used in that trial. Additionally, in a study of dexamethasone in bacterial meningitis in Vietnam, the HR was 0.43 in patients with microbiologically confirmed disease, and 0.59 in a study based in Europe, again in favour of dexamethasone [34, 35]. These analyses were all based on the intention-to-treat principle (including noncompliant patients), and it seems sensible to expect a similar rate of noncompliance in our study. Therefore, we believe a target hazard ratio of 0.7 in favour of dexamethasone to be reasonable for our trial.

To detect such a risk reduction of 30% with 80% power at the two-sided 5% significance level, a total of at least 247 deaths must be observed. Based on historical data and consultation with principal investigators from all study sites, the 10-week mortality risk in the control group is expected to be between 30% and 50% [38], and the target hazard ratio of 0.7 corresponds to absolute risk reductions in mortality from 30% to 22%, or from 50% to 38%. Assuming an overall 10-week mortality of at least 30% in our study population, recruitment of 824 patients is sufficient to observe the target number of deaths. Allowing for some loss to follow-up, the total sample size for this study is 880 patients.

A major aim of this trial is to generate robust evidence across both continents. To achieve this goal, we aim to recruit roughly similar numbers of patients from each continent.

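### The opportunistic-infection aim rests on an illness-or-death composite, although the plan already uses a competing-risk method for IRIS and relapse

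*Protocol article*

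**What the plan says.** Three places describe the quantity of interest without death in it:

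- Immunosuppression (under Potential harms of dexamethasone): "The incidence of other OIs is a secondary end point of the study".
- Secondary aims: the effect of dexamethasone on "the incidence of other opportunistic infections" is to be determined.
- Overview of the trial: the secondary end points include rates of new AIDS-defining illnesses and time to new neurologic events.

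The Secondary end points section has no separate entry for opportunistic infections. The nearest entry is time to new AIDS-defining illness or death until 10 weeks. New neurologic events are likewise joined with death.

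Analysis of secondary end points (under Adverse events) then fixes the method. The end points "time to new AIDS-defining illness or death and time to new neurologic event or death" get Kaplan-Meier curves and Cox models as for the primary end point. For IRIS and relapse the same paragraph specifies cause-specific proportional hazards models stratified by continent, "taking into account the competing risk of prior death", with cumulative incidence functions by arm.

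The paragraph before it plans an informal Fisher exact comparison of the proportion of patients with at least one event, overall and for each specific adverse event. Adverse event recording limits capture to grades 3 and 4.

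**The concern.** The aim asks about infection and the end point answers about infection or death. The composite hazard ratio is a weighted mean of the effects on its two components. If dexamethasone lowers mortality and raises infection, the two effects pull against each other, and the composite can read as neutral or favourable while infections increase. Immunosuppression is one of the harms the protocol itself discusses, and the mortality it expects is high enough for deaths to carry real weight in the composite.

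The composite can also mislead in the other direction. A mortality effect alone would move an end point that is labelled as infection.

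The protocol recognises the competing-risk problem for two non-fatal outcomes, IRIS and relapse, and gives no reason for handling new AIDS-defining illness differently.

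**Working it through.** **The plan's own figures.** Sample size and power considerations states "we believe a target hazard ratio of 0.7 in favour of dexamethasone to be reasonable for our trial" and "with 80% power at the two-sided 5% significance level, a total of at least 247 deaths must be observed". Schoenfeld's formula for a hazard ratio (HR) of 0.7 with 1:1 allocation gives 247 deaths, an exact match. Then 247/0.30 = 823.3, which rounds up to the stated 824. A hazard ratio of 0.7 takes 30% mortality to 1 − 0.7^0.7 = 22.1% and 50% to 1 − 0.5^0.7 = 38.4%, against the stated 22% and 38%.

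**Inputs for the masking check**

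- From the protocol: control 10-week mortality 30% or 50%; death HR 0.7; 880 patients at 1:1, so 440 per arm.
- Assumed, because the protocol gives no figures: control incidence of new illness as first event from 5% to 30%; illness HR 1.5, with 2.0 as a variant; constant, independent hazards over 10 weeks.

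**Formulas**

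- Control death hazard: h_d = −ln(1 − m). For m = 30% this is 0.357.
- Control illness hazard h_o: solved so that h_o/(h_d + h_o) × [1 − exp(−(h_d + h_o))] equals the assumed incidence.
- Composite HR = (0.7 h_d + HR_o h_o)/(h_d + h_o).
- Illness HR that brings the composite to exactly 1.0: 1 + 0.3 h_d/h_o.

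**Worked case: 30% mortality, 15% illness incidence, illness HR 1.5**

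- h_o = 0.195, so composite HR = (0.7 × 0.357 + 1.5 × 0.195)/0.552 = 0.98.
- Illness as first event rises from 15.0% to 22.6%, about 440 × (0.150 + 0.226) = 165 illness events in all.
- The composite has about 371 events and about a 2% chance of showing significant harm.
- A cause-specific Cox model has about 74% power: √(165/4) × ln 1.5 − 1.96 = 0.64, and Φ(0.64) = 0.74.
- A comparison of the two proportions has about 82% power if every illness is captured.

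**Range**

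| Control illness incidence | Composite HR, 30% mortality, illness HR 1.5 | Illness HR bringing composite to 1.0, 30% mortality | Composite HR, 50% mortality, illness HR 1.5 | Composite HR, 30% mortality, illness HR 2.0 |
|---|---|---|---|---|
| 5% | 0.82 | 2.75 | 0.78 | 0.89 |
| 10% | 0.91 | 1.85 | 0.84 | 1.04 |
| 15% | 0.98 | 1.55 | 0.90 | 1.16 |
| 20% | 1.04 | 1.40 | 0.95 | 1.26 |
| 30% | 1.14 | 1.25 | 1.04 | 1.41 |

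At illness HR 1.5 the composite stays below 1 for incidence up to 15% at 30% mortality, and up to 20% at 50% mortality. The masking fades as illness becomes more common or its hazard ratio larger.

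**Hand check.** With 30% dying first and 10% ill first, (0.30 × 0.7 + 0.10 × 1.5)/0.40 = 0.90, close to the 0.91 in the table. With no effect on death, (0.30 × 1.0 + 0.10 × 1.5)/0.40 = 1.125, so without a mortality benefit the composite points the right way. With death HR 1.2 and no effect on illness, (0.36 + 0.10)/0.40 = 1.15, an apparent infection signal produced by death alone.

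**The case against.** A reader might infer that infections and neurologic events are nowhere compared without death, so that the safety aim cannot be answered. The protocol does not support that. The Fisher comparison covers each specific adverse event by arm with no deaths added. Assessment of adverse events includes new AIDS-defining events, and the neurologic end point is built partly from named adverse events. Blindness and visual deficit have their own logistic regression. The monitoring committee sees serious and grade 3 and 4 events by arm. With near-complete follow-up, the proportion of randomised patients with an illness approximates the cumulative incidence with death as competing event. In the worked case that comparison has more power than the cause-specific model (82% against 74%). All of this stands.

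It narrows the point without removing it. The Fisher comparison is labelled informal and split by event type, and it takes no account of time at risk. Its recording is limited to grades 3 and 4. Nowhere does the protocol say that all the illnesses in Table 5 are pooled into one infection outcome. It is not presented as the analysis of a named secondary end point.

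It is also tempting to say that death makes up most of the composite. With no illness rate in the protocol, that is an assumption. At an assumed 30% incidence and 30% mortality, illness is the larger part (0.30/0.547 = 55% of control-arm first events).

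Two further objections carry some weight. Illness-or-death is a legitimate end point, and read beside the mortality result a discrepancy would be visible. Component breakdowns may also sit in an analysis plan that is not shown. However, the article does fix a method here, and that method does not match the stated aim. Finally, Secondary aims does not list neurologic events, so for those the composite is simply the defined end point.

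**Conclusion.** The point holds in limited form. As named time-to-event end points, both events are analysed only as composites with death, while the stated aim is the incidence of infections. Under the protocol's mortality assumptions and an illness HR of 1.5, the composite HR lies between 0.82 and 1.14 at 30% control mortality and between 0.78 and 1.04 at 50%. A mortality benefit at the target size can therefore offset a 50% rise in the illness hazard when control incidence is up to about 15%, and less so above that.

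The result depends on assumed illness rates and hazard ratios, on constant independent hazards, and on dexamethasone actually reducing death. The primary end point is unaffected. The change is worth making because a stated safety aim otherwise relies on a composite and an informal test. It does not follow that harm would go undetected.

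**What to change.** For new AIDS-defining illness, add a cause-specific proportional hazards model stratified by continent, and cumulative incidence curves by arm with death as the competing event, as already planned for IRIS and relapse. Name this as the analysis that answers the opportunistic-infection aim, and report the illness-or-death composite alongside. The same addition for new neurologic events is optional, for consistency. The cost is one or two extra model fits on data already collected, with no change to sample size, visits or patient care.
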